#### fNIRS data preprocessing

The relative concentration changes of oxygenated (O_2_Hb) and deoxygenated hemoglobin (HHb) will be calculated for every fNIRS channel. The fNIRS signal will be preprocessed by using the temporal derivative distribution repair [TDDR; 59] to correct for high-amplitude motion artifacts and by applying a bandpass filter of 0.005–0.2 Hz. To reduce low-amplitude motion artifacts, correlation-based signal improvement [CBSI; 60] will be used, which is based on the negative correlation between O_2_Hb and HHb and is considered one of the best artifact correction methods [61]. Next, remaining noisy channels will be interpolated by surrounding channels, and incorrectly solved trials as well as trials containing uncorrectable artifacts will be excluded.

To analyze the fNIRS data within a model-based approach, the peak latency of the hemodynamic response function will be determined by the overall maximum across channels, subjects, and conditions [in the interval between 4 and 10 s rounded to half a second; 25]. In the model-based approach, a general linear model will be computed for each channel, subject, and condition according to the hemodynamic response function. For every region of interest (10 ROIs: IFG, MFG, IPS, AG, SMG on the left and right hemisphere), the channel with the highest resulting beta value based on the grand average across conditions and subjects will be used for the statistical analysis of the neural data.

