### Arithmetic task

The arithmetic task will consist of two-digit addition and subtraction problems with two operands resulting in a two-digit solution [https://osf.io/6emdy/]. The carry and borrow operations will be manipulated categorically, i.e., addition problems with and without carrying (e.g., 51 + 43 vs. 58 + 36) as well as subtraction problems with and without borrowing (e.g., 94–43 vs. 94–36), and continuously, i.e., unit sum in addition (e.g., 14 in 58 + 36) and unit difference in subtraction (e.g.,– 2 in 94–36).

The stimulus set consists of 128 arithmetic problems with 32 trials per condition, i.e., addition with/without carrying and subtraction with/without borrowing. The stimulus generation will consider unit sum in addition and unit difference in subtraction to be relatively equally distributed. This means that addition problems (*a* + *b* = *r*) cannot be directly transformed by inversion into subtraction problems (*r*–*b* = *a*). Nevertheless, the numerical properties will be matched across conditions: *a* and *b* will be closely matched in their numerical magnitude and parity; the position of the larger operand will be counterbalanced; pure decades as well as ties within and between *a*, *b*, and *r* will be excluded [25, 42, for decades see 48, for ties see 49].

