Prior to the analyses of the arithmetic task, cognitive abilities will be analyzed: children and the elderly will be compared to young adults regarding processing speed (raw scores), working memory (ACC), and verbal and non-verbal intelligence (IQ scores) by two-sided Bayesian independent samples *t*-tests. Next, the arithmetic task will be analyzed in 3 age (children, adults, elderly) × 2 operation (addition, subtraction) × 2 complexity (with, without carry/borrow) Bayesian repeated measures ANOVAs [analysis over subjects, averaged over trials]. For effects with *BF*_*10*_ or *BF*_*01*_ ≥ 6, post-hoc two-sided tests will be conducted for the contrast children vs. young adults and the contrast young adults vs. the elderly by means of Bayesian independent samples *t*-tests, or for contrasting different conditions by means of Bayesian paired *t*-tests. Finally, multi-model Bayesian regressions will be conducted with the categorical predictor carry/borrow (with, without) and the continuous predictor unit sum/difference separately for addition and subtraction and for every age group [analysis over trials, averaged over subjects]. All confirmatory analyses will be conducted on the dependent variables RT, indicating behavioral performance, and beta values, indicating neural activation for each ROI separately (left/right IFG, MFG, IPS). Planned exploratory analyses will be conducted on ER and beta values for neural activation in the other ROIs (left/right AG, SMG).

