### Bayes factor design analysis

For sample size estimation, the sequential Bayes factor design with maximal *n* will be used [65, 66]. In this design, data collection (1) will start with a minimum sample size of *n*_*min*_ = 20 per group, (2) will continue until a *BF*_*10*_ or *BF*_*01*_ ≥ 6 is obtained for all effects of interest, or (3) will be stopped when a maximum sample size of *n*_*max*_ = 60 per group has been reached. The properties of the planned research design were estimated with Monte Carlo simulations according to Schönbrodt and Wagenmakers [65]: The minimum sample size was set for reducing false positive rates, and the maximum sample size was set to ensure feasibility, while 80% of studies with an infinite sequential sampling stop earlier than *n*_*max*_. If sampling is terminated because of reaching *n*_*max*_, only with a probability of 5% will the study obtain misleading evidence. This design detects an expected medium effect size of *δ* = 0.5 with a probability of 61% before the *n*_*max*_ is reached. The chosen medium effect size accounts for the bias of small samples in the reported large effect sizes ($\eta_{p}^{2}$ ≈ .5) for differences between children, young adults, and the elderly in the neural distance effect [67, for large effect sizes (*d* ≈ 1.2–1.6) see also for children vs. adults: 68, for younger adults vs. the elderly: 69].

The effects of interest according to the hypotheses include the main effect of age (ANOVAs) for RT and activation in left IFG, bilateral MFG, and left IPS according to H1; the main effect of complexity and the interaction effect of complexity and age (ANOVAs) for RT and activation in left IFG and bilateral MFG according to H2; the categorical carry/borrow effect and the continuous effect of unit sum/difference in each age group (regressions) in RT and neural activation in left IPS according to H3.

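### The neural H3 regressions need a beta per problem, but the fNIRS model is specified per condition, so the six continuous left-IPS effects are not identified as written

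*Protocol article*

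**What the plan says.** Under fNIRS data preprocessing, the first-level step is that "a general linear model will be computed for each channel, subject, and condition according to the hemodynamic response function". The Arithmetic task section fixes what a condition is: "32 trials per condition, i.e., addition with/without carrying and subtraction with/without borrowing". The same section makes the continuous variable a property of the individual problem, spread across values: "The stimulus generation will consider unit sum in addition and unit difference in subtraction to be relatively equally distributed".

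Under Statistical data analysis, H3 is addressed as follows: "multi-model Bayesian regressions will be conducted with the categorical predictor carry/borrow (with, without) and the continuous predictor unit sum/difference separately for addition and subtraction", done for each age group and labelled as "analysis over trials, averaged over subjects". That section then names reaction time and the beta values as the outcomes of all confirmatory analyses.

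Under Bayes factor design analysis, the H3 effects of interest are "the categorical carry/borrow effect and the continuous effect of unit sum/difference in each age group (regressions) in RT and neural activation in left IPS". Sampling continues until every effect of interest reaches a Bayes factor of 6 in either direction, or until 60 subjects per group. In the Introduction, the only neural prediction under H3 is that the continuous effects rely on left IPS in all age groups.

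**The concern.** The outcome is produced at one level and analysed at another. The first-level model gives a beta for a whole condition, whereas the H3 regression needs one for each problem, because unit sum and unit difference vary between problems within a condition. Nothing in the article bridges the two: it mentions neither a single-trial model nor a modulator.

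The neural half of H3 is at stake. If the preprocessing section is followed literally, the regression that is meant to separate a categorical from a continuous effect in left IPS cannot separate them. These effects also belong to the set on which early stopping depends. In a registered report, the choice of how to obtain problem-level information should be fixed in advance. Inter-trial intervals are 4–7 s and the haemodynamic peak is sought between 4 and 10 s, so responses to neighbouring trials may overlap, and different single-trial methods may give different answers.

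**Working it through.** **The plan's own figures.** Four conditions × 32 trials = 128 problems, which also equals 4 runs × 32, as stated. Per operation this is 2 × 32 = 64. The stated 61% chance of detecting δ = 0.5 before the maximum sample size was also simulated (two-sided Bayesian t-test, Cauchy scale 0.707, threshold 6, checked at every n from 20 to 60 per group, 20,000 runs). The result was 60.7%, so that figure reproduces. It has no bearing on the present point, which concerns the unit of analysis.

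**Number of effects.** H3 effects of interest: 2 predictors × 2 operations × 3 age groups × 2 outcomes (reaction time, left IPS) = 24. Of these, 12 are in left IPS: 6 continuous and 6 categorical.

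**Assumption for the design matrices.** The article does not list the unit values. With pure decades excluded, I take unit sums 2–9 and 11–18, and unit differences 1 to 8 and −1 to −8, each value used four times (16 values × 4 = 64). The collinearity result for condition-level betas does not depend on this assumption; the correlation for problem-level betas does.

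**Design with condition-level betas.** Columns: intercept, carry/borrow, mean unit sum or difference.
- Addition: rows (1, 0, 5.5) and (1, 1, 14.5). Mean unit sum = 5.5 + 9 × carry, an exact linear function of carry.
- Subtraction: rows (1, 0, 4.5) and (1, 1, −4.5). Mean unit difference = 4.5 − 9 × borrow.
- In both there are 2 rows for 3 coefficients, rank 2, and the predictors correlate at +1 or −1.
- Without averaging over subjects, at 60 per group, there are 60 × 2 = 120 rows. The rank is still 2 of 3, because the planned unit value is constant within a condition.

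**Design with one beta per problem.**
- 64 rows per operation and age group, rank 3 of 3, and 64 − 3 = 61 residual degrees of freedom.
- Between-condition variance of the unit value = (9/2)² = 20.25. Within-condition variance of eight consecutive integers = (8² − 1)/12 = 5.25. Total = 25.5.
- r² = 20.25/25.5 = 0.794, so |r| = 0.891. Variance inflation factor = 1/(1 − r²) = 25.5/5.25 = 4.86.

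Both effects are then estimable, although the predictors remain strongly correlated.

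**The case against.** The best defence is that the article already points to trial-level betas. The regressions are labelled as run over trials with subjects averaged, and the ANOVAs the other way round, for the same outcomes. Individual trials are also excluded from the fNIRS analysis. On that reading the article has merely left out a first-level sentence, as a condensed article may, and the collinear regression is not the one planned. This is plausible as to intent. But the preprocessing section does not stay silent on the unit. It states one, and that unit conflicts with the regression, so one of the two statements has to change. A condition-level beta also pools individual trials, so the trial exclusions do not settle the matter.

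Three stronger readings are tempting, and the document does not support them:

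- A reader might infer that all 12 left-IPS effects under H3 lose any test. Only the 6 continuous ones do. Condition-level betas still allow a with/without comparison in left IPS, since the complexity ANOVA covers IPS and paired tests are foreseen.
- A reader might infer that the stopping rule fails altogether. It does not, because sampling ends at 60 per group whatever the Bayes factors.
- A reader might infer that the regressions must be replaced by subject-level tests on a modulator, at no loss of precision. The article gives neither reaction times nor noise levels from which to establish that. Such a switch would also drop the planned multi-model comparison and its stated regression prior, when one beta per problem is sufficient.

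**Conclusion.** The point holds as an internal contradiction between the first-level model and the H3 regressions. With betas as the preprocessing section defines them, the 6 continuous left-IPS effects, which are the whole of H3's neural prediction, are not identified. The 6 categorical effects survive only as a simple contrast. The Bayes factor criterion cannot be evaluated for these effects as specified, so early stopping is blocked.

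The non-identification rests only on the article's own definitions of condition and of the first-level model. The correlation of about 0.89 after repair rests on the assumed even spread of unit values. The ANOVAs for H1 and H2 need only condition-level betas, and the reaction-time regressions for H3 use an outcome that exists for every trial, so both stand.

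**What to change.** Before data collection, reconcile the sections fNIRS data preprocessing, Statistical data analysis and Bayes factor design analysis. The smallest change is to state under preprocessing that, for the H3 regressions, the first-level model yields one beta per problem for each subject and channel. These betas are averaged over subjects and entered in the regressions already planned. The single-trial estimation method should be named, because the short inter-trial intervals make the choice matter.

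An acceptable alternative keeps the four-condition model and adds a unit-sum modulator for addition and a unit-difference modulator for subtraction. The resulting subject-level tests, per operation and age group, are then named as the neural H3 effects of interest. This departs further from the plan, since it replaces the multi-model regression and its prior for the neural outcome.

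The cost is wording and some extra first-level analysis. Single-trial betas will be noisier than condition betas, and the two predictors will remain correlated. No new data are needed.

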#### Statistical data analysis

This study applies Bayesian hypothesis testing and thus Bayes factors (*BF*) are calculated that determine how much more likely the observed data will be under the alternative hypothesis (H_1_) as compared to the null hypothesis (H_0_) for *BF*_*10*_ (evidence for a difference when *BF*_*10*_ > 1) and vice versa for *BF*_*01*_ (evidence for no difference when *BF*_*01*_ > 1), whereby *BF*_*01*_ = 1/*BF*_*10*_ [62]. *BF*s can be interpreted to provide anecdotal evidence for 1–3, moderate evidence for 3–10, strong evidence for 10–30, and very strong evidence for 30–100, and extreme evidence above 100 in favor of one hypothesis [63, 64].

The statistical analyses in terms of Bayesian *t*-tests, Bayesian ANOVAs and Bayesian linear regressions will be performed with JASP (Jeffreys’s Amazing Statistics Program, JASP Team, 2016). The analysis prior will be set to a Cauchy prior scale of 0.707 in Bayesian *t*-tests, reflecting that H_0_ and H_1_ are equally likely to occur, to the default Cauchy prior of *r* = 0.5 for the fixed effects in Bayesian ANOVAs, to the default Jeffreys–Zellner–Siow prior of *r* = 0.354 for regression coefficients, and to a uniform model prior in Bayesian linear regressions. Bayesian ANOVAs and linear regressions will set out to compare each model to the null model and Bayesian model averaging will compare the models with the respective effect to equivalent models without the effect (analysis suggested by [name]).

Prior to the analyses of the arithmetic task, cognitive abilities will be analyzed: children and the elderly will be compared to young adults regarding processing speed (raw scores), working memory (ACC), and verbal and non-verbal intelligence (IQ scores) by two-sided Bayesian independent samples *t*-tests. Next, the arithmetic task will be analyzed in 3 age (children, adults, elderly) × 2 operation (addition, subtraction) × 2 complexity (with, without carry/borrow) Bayesian repeated measures ANOVAs [analysis over subjects, averaged over trials]. For effects with *BF*_*10*_ or *BF*_*01*_ ≥ 6, post-hoc two-sided tests will be conducted for the contrast children vs. young adults and the contrast young adults vs. the elderly by means of Bayesian independent samples *t*-tests, or for contrasting different conditions by means of Bayesian paired *t*-tests. Finally, multi-model Bayesian regressions will be conducted with the categorical predictor carry/borrow (with, without) and the continuous predictor unit sum/difference separately for addition and subtraction and for every age group [analysis over trials, averaged over subjects]. All confirmatory analyses will be conducted on the dependent variables RT, indicating behavioral performance, and beta values, indicating neural activation for each ROI separately (left/right IFG, MFG, IPS). Planned exploratory analyses will be conducted on ER and beta values for neural activation in the other ROIs (left/right AG, SMG).

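### The neural H3 regression needs item-level betas that the stated GLM does not produce, and every H3 regression has 64 rows, so a null effect beside an absent or weak partner cannot reach BF01 ≥ 6 at any planned sample size

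*Protocol article*

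**What the plan says.** All references are to the protocol article.

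- **Items (Arithmetic task).** "The stimulus set consists of 128 arithmetic problems with 32 trials per condition". The four conditions are addition with and without carrying and subtraction with and without borrowing.
- **H3 analysis (Statistical data analysis).** The regressions for H3 are run "separately for addition and subtraction and for every age group [analysis over trials, averaged over subjects". Each of them is fitted "with the categorical predictor carry/borrow (with, without) and the continuous predictor unit sum/difference". The ANOVAs for H1 and H2, by contrast, are labelled "analysis over subjects, averaged over trials". RT and the betas are the confirmatory outcomes.
- **Prior and effect-level evidence (same section).** The prior is set "to the default Jeffreys–Zellner–Siow prior of *r* = 0.354 for regression coefficients" with a uniform model prior, and "Bayesian model averaging will compare the models with the respective effect to equivalent models without the effect".
- **Level of the betas (fNIRS data preprocessing).** "a general linear model will be computed for each channel, subject, and condition according to the hemodynamic response function".
- **Stopping rule (Bayes factor design analysis).** Sampling runs from 20 to at most 60 per group and stops earlier only if every effect of interest reaches BF10 or BF01 of at least 6. The list of effects includes "the categorical carry/borrow effect and the continuous effect of unit sum/difference in each age group (regressions) in RT and neural activation in left IPS".

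**The concern.** The confirmatory neural prediction of H3 is that the continuous effect relies on left IPS in every age group. Testing it needs a beta for each problem, or some other estimate that varies with unit sum inside a condition. The preprocessing section describes neither.

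The sequential design adds participants to gain evidence, but the H3 regressions gain no rows from them. If an H3 effect is truly absent and its partner predictor is absent or weak, more people cannot bring the Bayes factor to the plan's threshold. All H3 effects sit in the set that must be decisive before sampling stops, so one such effect costs the full sample and still ends undecided. The operating characteristics in the design analysis do not describe these regressions.

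**Working it through.** **1. The plan's own figure.** The design analysis states a 61% probability of detecting δ = 0.5 before the maximum sample. Simulating a sequential two-sided, two-sample Bayesian t-test (Cauchy 0.707, 20 to 60 per group in steps of 1, bound 6, 10,000 runs) gives 60.5%; a paired test gives 89%. The figure therefore describes a between-group t-test. The article gives no corresponding figure for the item regressions.

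**2. Neural outcome.** Each operation has two conditions. Condition-level betas averaged over subjects give 2 values per operation and age group. A regression on carry/borrow and unit sum/difference has an intercept and two slopes, and with two points the unit-sum values are a linear function of carry/borrow. The slope is not identified.

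**3. Number of rows and of tests.** 2 conditions × 32 problems = 64 item means per regression, at n = 20 and at n = 60. The H3 effects in the stopping rule number 2 predictors × 2 operations × 3 age groups × 2 outcomes = 24 Bayes factors.

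**4. Ceiling on evidence for the null.** For p predictors and N rows,

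BF10 = ∫ (1+g)^((N−p−1)/2) · (1+g(1−R²))^(−(N−1)/2) · π(g) dg, with g ~ InvGamma(1/2, N·r²/2), r = 0.354, N = 64.

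- At R² = 0, one predictor: BF10 = 0.2551, so BF01 = 3.92. Two predictors: BF10 = 0.0945.
- Inclusion BF01 for one predictor, four models with equal prior weight: (1 + 0.2551)/(0.2551 + 0.0945) = 3.59.
- Simulated data with neither effect: maximum 3.6, median 2.7, and BF01 ≥ 6 never occurred.

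Under the null, R² has a distribution that depends only on the row count, so n does not enter: the median single-predictor ln BF10 was −1.2 at n = 20, 40 and 60. For comparison, the one-predictor ceiling is 5.30 at N = 128 and 6.20 at N = 180.

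**5. When one or both effects are real.** This needs an item grid, which the article does not print. Assumption: unit sums 2–9 and 11–18, four items each. The variance of unit sum is then 25.5, of which 20.25 lies between carry classes, so r = √(20.25/25.5) = 0.89 and VIF = 1/(1 − 0.794) = 4.9. Unit differences of −8 to −1 and 1 to 8 give the same values. Results from 2,000 to 3,000 runs per scenario:

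| Item R² | Only carry real: unit sum reaches BF01 ≥ 6 | Both real and equal: both reach BF10 ≥ 6 |
|---|---|---|
| 0.1 | 0% | under 1% |
| 0.2 | 0% | under 1% |
| 0.4 | about 6% | under 1% |
| 0.6 | 51% | under 1% |
| 0.7 | 67% | about 7% |
| 0.8 | 78% | about 49% |
| 0.9 | 87% | about 97% |

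With both effects real and equal at R² = 0.6, one of them is declared absent in about 11% of runs.

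**6. Does evidence grow with participants?** Assume a carry effect of 1 s, no unit-sum effect, and a trial SD of 2 s.

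- Item SD 0.3 s: median ln BF10 for carry is 16.9, 23.4 and 26.8 at n = 20, 40 and 60, and unit sum reaches BF01 ≥ 6 in 16%, 42% and 53% of runs.
- Item SD 0.5 s: unit sum reaches it in 3%, 10% and 11%.
- Item SD 0.1 s: 37%, 65% and 75%.
- Carry effect of only 0.3 s: 0% at every n, for each of the item SDs 0.1 and 0.5 s.

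**The case against.** Several stronger readings are tempting, and the document does not support them.

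- **That the Bayes factors cannot accumulate with participants.** Averaging over more people makes the item means more precise. BF10 then rises, and so does BF01 when the partner predictor is strong (step 6). Only null evidence beside an absent or weak partner stays put.
- **That BF01 ≥ 6 is usually out of reach.** The 3.92 ceiling compares one predictor with the null, whereas the plan uses inclusion Bayes factors over matched models. With a strong categorical effect, BF01 ≥ 6 is reached in 51% to 87% of runs (item R² 0.6 to 0.9). The article gives no item R², so no frequency can be claimed, and means over 20 to 60 people could have a high one.
- **That H3 predicts zero effects.** It describes the effects as more categorical in children and more continuous in the elderly, which is relative. For left IPS it predicts that a continuous effect is present.
- **That the stopping rule is blocked.** The cap of 60 per group is an explicit exit. The cost is sample size and an inconclusive result, and the study remains valid.
- **That the neural test is impossible in principle.** The ANOVAs, which also cover betas, are labelled as averaged over trials, so trial-level betas may have been intended. But the preprocessing section states another level, so this is a conflict between stated passages and not merely detail left out of an article.

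The correlation of 0.89 rests on an assumed grid; the article says only that unit sums and differences are spread fairly evenly. The ceilings in step 4 do not depend on the grid.

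**Conclusion.** The point holds in two parts.

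The neural H3 regression cannot be carried out with the betas as defined, and the two sections must be reconciled. This rests on the text alone and is the firmer part.

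The H3 regressions are also poorly matched to the stopping rule. With neither effect present, the inclusion BF01 stays at or below about 3.6 against a threshold of 6, at any n from 20 to 60. With a weak partner predictor the threshold is almost never met. Any one such effect among the 24 takes sampling to the maximum and remains undecided. How likely this is depends on effect sizes that the article does not give. On the assumed grid, the young-adult prediction that both effects are present would rarely be confirmed for both when they are of equal size, unless item R² is well above 0.6.

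The lack of a direct age comparison is a weakness and not an error: H3 contrasts age groups, while the plan fits each group separately.

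**What to change.** 1. **Left IPS.** Enter unit sum/difference as a parametric modulator within each condition of each participant's GLM, or estimate trial-level betas, and test the result across participants. State the choice in the preprocessing section so that it agrees with the statistical section.
2. **RT.** Replace the item-mean regressions with a trial-level mixed model that has participant and item effects and age × predictor terms. A between-group Bayesian t-test on participant slopes is not adequate for null evidence: with the plan's 0.707 prior its BF01 ceiling is 5.14 at 60 per group. A one-sample test within a group has a ceiling of 4.3 at n = 20 and passes 6 only at about n = 43.
3. **Stopping rule.** Remove the 64-item regressions from the effects that must all reach a Bayes factor of 6. If the replacement tests are put in their place, simulate their operating characteristics first. The mixed model was not simulated here.
4. **Collinearity.** Report the correlation between the two predictors in the actual stimulus list.

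The cost is modest extra analysis work on data the study collects anyway. Single-participant slopes will be noisy, but evidence from them grows with the number of participants.
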